2. Subcutaneous tissue closure is not necessary, but can be performed based on the investigator’s judgment.

3. Skin closure can be performed using stapler or non-absorbent sutures whichever is a general method of each institution.

B. Reasons for the choice

The reasons are stated under the section ‘Background.’

1. **Observation Items, Clinical Test Items, Observation and Test Methods**

| Observation Items | Observation and Test Methods |
| --- | --- |
| 1-year cumulative incidence of incisional hernia after surgery | Subjects are advised to make outpatient visits for Year 1 after surgery. Visits made between 9 and 15 months after surgery can be counted as Year 1 visit. Investigators will conduct a physical checkup to diagnose incisional hernia. Investigators can refer to post-surgery image test result. If investigators are not sure of incisional hernia, a diagnostic test can be carried out. Subjects will be censored if they underwent midline laparotomy once again after receiving the surgery from this study, are dead or lost to follow-up at the time of event. Investigators will not be reminded of group allocation and will be blinded until Year 1 visit is completed. |
| 4-week cumulative incidence and types of surgical site infection after surgery | Subjects are advised to make outpatient visits for Week 4 after surgery. Visits made between 3 to 5 weeks after surgery can be counted as Week 4 visit. Investigators will conduct a physical checkup to diagnose surgical site infection. If subjects make outpatient visits before Week 4 after surgery, investigators should check for surgical site infections and their types. All information obtained from visits made immediately after surgery up to Week 4 will be used to diagnose all surgical site infections. CDC standards will be used to determine surgical site infections and their types. (https://www.cdc.gov/nhsn/PDFs/pscManual/17pscNosInfDef_current.pdf). If any surgical site infection is observed according to CDC standards, the patient will be judged to have a surgical site infection. Investigators will not be reminded of group allocation. |

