| 4-week cumulative incidence of wound dehiscence after surgery | Subjects are advised to make outpatient visits for Week 4 after surgery. Visits made between 3 to 5 weeks after surgery can be counted as Week 4 visit. Investigators will conduct a physical checkup to diagnose wound dehiscence. Wound dehiscence is defined as all wound dehiscence in any depth and length. If subjects make outpatient visits before Week 4 after surgery, investigators should check for wound dehiscence. All information obtained from visits made immediately after surgery up to Week 4 will be used to calculate all cumulative incidence. Events that will be included in the calculation of cumulative incidence will be: when wound dehiscence is observed even just once until Week 4 after surgery; when removal of stapler or suture is impossible at Week 4; or wound dehiscence is observed during follow-up after stapler or suture was removed at Week 4. |
| Wound dehiscence incidence at week 4 after surgery | Subjects are advised to make outpatient visits for Week 4 after surgery. Visits made between 3 to 5 weeks after surgery can be counted as Week 4 visit. Investigators will conduct a physical checkup to diagnose wound dehiscence. Wound dehiscence at Week 4 is defined as: when a wound is expanded at Week 4 evaluation; when removal of stapler or suture is impossible; or wound dehiscence is observed during follow-up after stapler or suture was removed at Week 4. If wound dehiscence was observed before Week 4 but it disappeared at Week 4, the subject is not counted to have wound dehiscence at Week 4 after surgery. When stapler or suture is removed at Week 4 visit, a follow-up visit or phone counseling is required. If no wound dehiscence is discovered from the follow-up visit or phone counseling, the subject is not counted to have wound dehiscence. However, if wound dehiscence is discovered from the follow-up visit or phone counseling, the subject is counted to have wound dehiscence. |
| BPI-K Score | BPI-Korean version is used at baseline, Day 2 and Day 4 after surgery. |
| NRS Pain Score | Pain scores, measured by NRS which is a usual way of monitoring surgical patients, and record times are collected from immediately after surgery until 10pm of Day 4 after surgery. |

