| Demographics of subjects, surgical information | Date of birth, height, weight, current smoker, medical history, pre- and postoperative chemotherapy, corticosteroids, previous abdominal surgery, ASA classification, type of surgery, suture length, wound length, operation time, antibiotic prophylaxis, intra-abdominal drain, subcutaneous drain, DVT prophylaxis, Patient controlled analgesia (Y/N, type IV or epidural), wound anesthetics infiltration system, perioperative complications, transfusion, postoperative radiation, ICU care |
| Incidence, types, grades and relevance of adverse events excluding incisional hernia, pains, surgical site infections, and wound dehiscence | Adverse events are collected by listening to the subject’s medical history and conducting a physical checkup during hospitalization for surgery, Week 4 and Year 1 visits after surgery. All visits and medical records until Year 1 after surgery will be used. CTCAE ver 4.0 will be used to grade each adverse event. |

1. **Efficacy Evaluation Standards, Evaluation Methods**

| Purpose | Analysis and Evaluation Methods | Cohorts for analysis |
| --- | --- | --- |
| Compare cumulative incisional hernia incidence until Year 1 after surgery between A+B arm and C+D arm. | Cumulative incidence of incisional hernia of A+B arm will be compared with that of C+D arm using chi-square or Fisher's exact test. P value 0.05 will be used to determine significance. | All patients who undergo surgery. Patients who do not have incisional hernia will be censored at last visit. Incidence will be estimated from time-occurrence curve. |
| Compare incisional hernia incidence curve by time between A+B arm and C+D arm. | Time-occurrence curve of incisional hernia will be depicted using Kaplan-Meier method and be compared between A+B vs C+D arm using log-rank test. P value 0.05 will be used to determine significance. | All patients who undergo surgery |
| Compare cumulative incidence of surgical site infections and their types until Week 4 after surgery between A+B arm and C+D arm. | Cumulative incidence of SSI of A+B arm will be compared with that of C+D arm using chi-square or Fisher's exact test. P value 0.05 will be used to determine significance. Type of SSI will be summarized. | Patients who undergo surgery |

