| Compare cumulative wound dehiscence incidence at Week 4 after surgery between A+B arm and C+D arm. | Cumulative incidence of wound dehiscence of A+B arm will be compared with that of C+D arm using chi-square or Fisher's exact test. P value 0.05 will be used to determine significance. | Patients who undergo surgery and complete week 4 visit |
| Compare wound dehiscence incidence at Week 4 after surgery between A+B arm and C+D arm. | Incidence of wound dehiscence of A+B arm will be compared with that of C+D arm using chi-square or Fisher's exact test. P value 0.05 will be used to determine significance. | Patients who undergo surgery and complete week 4 visit |
| Compare BPI-K scores that are obtained at baseline, Day 2 and Day 4 after surgery between A+B arm and C+D arm. | BPI score (total and each question) obtained at baseline will be compared between A+B vs C+D arm. BPI score (total and each question) obtained at postoperative day 2 will be compared between A+B vs C+D arm. BPI score (total and each question) obtained at postoperative day 4 will be compared between A+B vs C+D arm. Student t-test will be used. P value 0.05 will be used to determine significance. If BPI score at baseline is imbalanced between arms, change of BPI score (from baseline to postoperative day 2, 4) will be compared. | Patient who undergo surgery and complete BPI |
| Compare NRS pain scores collected until Day 4 after surgery between A+B arm and C+D arm. | NRS collected for postoperative 4 days will be compared between A+B vs C+D arm using linear mixed model. P value 0.05 will be used to determine significance. | Patients who undergo surgery and NRS are measured |
| Compare cumulative incidence and types of surgical site infections until Day 4 after surgery between A+C arm and B+D arm (depending on whether subcutaneous drain is inserted or not) | Cumulative incidence of SSI of A+C arm will be compared with that of B+D arm using chi-square or Fisher's exact test. P value 0.05 will be used to determine significance. Type of SSI will be summarized. | Patients who undergo surgery |
| Compare cumulative wound dehiscence incidence at Week 4 after surgery between A+C arm and B+D arm (depending on whether subcutaneous drain is inserted or not) | Cumulative incidence of wound dehiscence of A+C arm will be compared with that of B+D arm using chi-square or Fisher's exact test. P value 0.05 will be used to determine significance. | Patients who undergo surgery and complete week 4 visit |

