**(2) Removal of subjects from study**

A. Subjects can remove from study unconditionally while they are participating in the study.

B. Subjects are removed if they do not undergo midline laparotomy. No follow-up will be performed afterwards.

C. If incisional hernia is diagnosed in 4 weeks after surgery, no follow-up will be performed afterwards. In this case, subjects are considered to have completed the trial participation. If incisional hernia is diagnosed when 4 weeks have not elapsed after surgery, follow-up observations will be made until Week 4 after surgery.

D. If subjects undergo another abdominal midline laparotomy after surgery, the subject will be withdrawn from the trial. No follow-up will be performed afterwards.

E. If it is judged that a subject is no longer able to participate in the trial due to the subject’s noncooperation, the principal can decide to discontinue the subject’s participation.

F. If a subject is withdrawn from the trial, data collected until the time of withdrawal are used for the trial.

1. **Evaluation Standards, Methods and Reporting of Safety Including Side Effects**

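### The Week-4-completer cohort for cumulative wound dehiscence contradicts the endpoint's own event rule and, with the repeat-laparotomy rules, drops early re-operated fascial failures from the suture comparisons in the efficacy table

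*Protocol*

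**What the plan says.** Five statements in the protocol bear on a patient whose fascia gives way early and is re-closed through the midline.

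- **Withdrawal** (Removal of subjects from study, item D): "If subjects undergo another abdominal midline laparotomy after surgery, the subject will be withdrawn from the trial. No follow-up will be performed afterwards". No reason for the repeat operation is distinguished.
- **Data before withdrawal** (same section, item F): "data collected until the time of withdrawal are used for the trial".
- **Primary endpoint** (Observation Items table, 1-year incisional hernia): "Subjects will be censored if they underwent midline laparotomy once again after receiving the surgery from this study". The primary row of the efficacy table agrees: "All patients who undergo surgery. Patients who do not have incisional hernia will be censored at last visit".
- **Dehiscence definition** (Observation Items table, 4-week cumulative incidence): "Wound dehiscence is defined as all wound dehiscence in any depth and length". An event arises, among other ways, "when wound dehiscence is observed even just once until Week 4 after surgery", and information from every visit since surgery is to be used.
- **Dehiscence cohort** (Efficacy Evaluation Standards table): all four dehiscence rows, cumulative and at Week 4, by suture and by drain, use "Patients who undergo surgery and complete week 4 visit".

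Two further rows matter. The SSI rows of the same table use every operated patient, with no visit condition. The adverse-event row leaves out wound dehiscence.

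**The concern.** A cumulative endpoint that counts a single early observation should not require attendance at a later visit. Here the requirement is tied to outcome: a serious early closure failure can lead to a second midline laparotomy, which triggers withdrawal, which prevents the Week 4 visit, which removes the patient from the cohort. In the hernia analysis she leaves the risk set without an event. Both routes treat as neutral a departure caused by failure of the randomised closure.

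The protocol lists increased wound dehiscence among the potential risks of SS-PDS. If such failures differ between arms, the planned suture comparisons could miss the difference, and the arm with more of them need not look worse.

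**Working it through.** **1. Following one patient through the text.** Suppose fascial dehiscence is seen on day 8 and re-closed through the midline that day.

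| Planned comparison | Treatment as written |
|---|---|
| 1-year hernia, chi-square or Fisher, and log-rank (A+B vs C+D) | censored, no event |
| Cumulative dehiscence (A+B vs C+D; A+C vs B+D) | an event by definition, but outside the cohort |
| Dehiscence at Week 4 (both contrasts) | outside the cohort |
| Adverse events, efficacy table | dehiscence left out |
| Suture-related adverse events, safety section | may be counted, but the contrast named is A+C vs B+D (drain) |

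No A+B vs C+D row of the efficacy table counts her. The second table row is the contradiction: the event rule and item F would count her, while the cohort column removes her.

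**2. The plan's own figure.** Inputs from Target Sample Size: 0.13 versus 0.03, one-sided alpha 0.05, power 0.80, drop-out 0.06, 87 per arm. With the arcsine formula, h = 2·asin(√0.13) − 2·asin(√0.03) ≈ 0.390 and n = 2·[(1.645 + 0.842)/h]² ≈ 81.5. Then 81.5/0.94 = 86.7, or 87. The figure is reproduced, and this point does not depend on it.

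**3. Expected counts.** Hernias with SS-PDS: 0.03 × 87 = 2.6. Control: 0.13 × 87 = 11.3.

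The protocol gives no rate r for fascial dehiscence re-operated before the Week 4 visit. The range below is an assumption.

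| r | Per arm, 87r | Both arms, 174r | Chance of at least one, 1 − (1 − r)^174 |
|---|---|---|---|
| 0.5% | 0.4 | 0.9 | 58% |
| 1% | 0.9 | 1.7 | 83% |
| 2% | 1.7 | 3.5 | 97% |
| 3% | 2.6 | 5.2 | over 99% |

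**4. Sensitivity of a hernia result, on assumed counts.** Take 82 evaluable per arm (87 × 0.94 = 81.8) and results near the design: 3/82 versus 11/82, one-sided Fisher p = 0.024. Now place k re-operated failures in the SS-PDS arm only, which is an unfavourable placement chosen for illustration.

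| k | Left out: 3/(82 − k) vs 11/82 | Counted: (3 + k)/82 vs 11/82 |
|---|---|---|
| 1 | 0.025 | 0.051 |
| 2 | 0.026 | 0.093 |
| 3 | 0.028 | 0.153 |

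**5. Cumulative dehiscence, on assumed counts.** If 9 completers in an arm of 87 have dehiscence and 3 more patients are re-operated before the visit, the rate is 9/84 = 10.7% as the cohort is written and 12/87 = 13.8% if they are counted.

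**The case against.** A reader might infer that these failures are counted nowhere in the trial, or are certainly excluded from every dehiscence analysis. The protocol does not support either reading.

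- Item F keeps data collected before withdrawal, and a dehiscence that prompts re-operation is normally seen before it. Read with the event rule, this favours counting the case, so the text is contradictory rather than clear in excluding her.
- The safety section compares suture-related adverse events, overall and grade 3 or above, without leaving out dehiscence. The interim safety review looks at dehiscence in the first 10 A+B subjects, and all adverse events are collected and reported to the IRBs yearly.
- The visit window is wide: "Visits made between 3 to 5 weeks after surgery can be counted as Week 4 visit". A patient re-operated after attending in week 3 is already a completer.

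All of this stands, but none of it supplies the missing suture comparison. Retaining data does not place a patient in a cohort defined by a visit she did not attend. The safety comparisons name the drain contrast, the interim review covers one arm, and annual reporting is not a comparison.

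The primary endpoint can also be defended. Incisional hernia is the stated target, and after re-closure the randomised closure is no longer under observation. Re-laparotomy for a hernia already diagnosed loses nothing, because the diagnosis is the event. This argues against redefining the primary endpoint, and that argument is accepted. It does not make the censoring uninformative.

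Supplementary analyses are often left to a SAP. The cohorts, the censoring and the withdrawal rule, however, are fixed in this protocol.

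**Conclusion.** The point holds as an internal contradiction with a consequence. The completer cohort conflicts with the cumulative dehiscence event rule and with item F. Combined with withdrawal and censoring that ignore the reason for repeat laparotomy, it leaves an early re-operated fascial failure outside every A+B vs C+D comparison in the efficacy table. That is certain from the wording only for re-operation before the Week 4 visit.

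The size is not known. At assumed rates of 0.5% to 3%, 0.4 to 2.6 patients per arm are affected, and only the top of that range matches the 2.6 hernias expected with SS-PDS. The p-value shifts assume every such failure falls in one arm, which nothing in the protocol suggests. They show only that, with so few events, a single patient's classification could matter.

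**What to change.** 1. In the efficacy table, change the cohort for both cumulative dehiscence comparisons (A+B vs C+D and A+C vs B+D) to all operated patients, as in the SSI rows. State that any dehiscence observed before withdrawal or before a missed Week 4 visit counts as an event. The rows for dehiscence present at Week 4 describe status at that visit and can keep their cohort.
2. Keep the primary hernia endpoint as defined. Record the reason for any repeat midline laparotomy, and pre-specify a supplementary analysis, reported beside the primary, that counts re-laparotomy for fascial dehiscence as a closure-failure event.

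The cost is wording and one data field, with no added visit: the reason is known when the patient is withdrawn. There are two downsides. The supplementary composite is broader than hernia alone. The enlarged dehiscence cohort will include some patients observed for less than the full period to Week 4, and their number should be reported by arm.

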**(1) Causality Evaluation**

A. Investigators will determine that there is or there is no causal relationship with the SS-PDS use (including control group’s suture). If it is difficult for the investigator to make a judgment, it will be judged to have a causal relationship.

B. Causality will not be evaluated for the use of subcutaneous drain.

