Incisional hernia is a type of hernia that forms at the site of surgical incision [PMID: 19495920]. Incisional hernia is a common complication of abdominal surgery with an incidence of 10-23%. The incidence is known to reach as high as 38% in high-risk group patients of old age, obesity, chronic obstructive pulmonary diseases, malnutrition, and abdominal aneurysm, etc. [PMID: 21254041]. Operative risk factors influential to the incidence of incisional hernia are incision types, sizes and abdominal closure [PMID:10195729, 3159324, 3954314, 2804595]. Incisional hernia degrades the quality of life and incurs a lot of cost [PMID:26206646].

Appropriate methods of abdominal fascia closure are suggested in various reviews and guidelines [PMID10714638, 15796944, 12594682, 11379640, 9926810, 20395846]. According to meta-analysis, incisional hernia incidence was lower with running suture using monofilament suture than interrupted suture because it is absorbed slower [PMID: 20395846,12594682, 26188742, 19917943]. However, more than 10% of the patients still experience incisional hernia after abdominal surgery even when adequate sutures and methods are used [PMID: 26188742]. Therefore, it is necessary to improve the method of abdominal fascia closure.

Barbed suture is a type of suture that has barbs on its surface. In many cases, similar or better closure results are obtained with barbed suture than those without barbs [PMID: 28603661]. STRATAFIX Symmetric PDS Plus (SS-PDS) is one of the barbed sutures that can be used for closure of high pressure sites such as fascia. SS-PDS demonstrates superior or similar results compared to conventional sutures without barbs in terms of strength and the ability to hold the tissues tight [PMID: 28603661].

Opinions vary as to whether subcutaneous drain insertion at the time of abdominal closure reduces wound dehiscence [PMID: 19442311]. Several studies report that subcutaneous drain insertion reduces wound complications [PMID: 24952366].

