A. investigators: investigators at each institution can view CRF and check randomization results without a separate approval procedure.

B. study subjects: if investigators see it necessary for medical purposes, they can inform the subjects of the randomization results after approval by the principal investigator.

(8) Interim Analysis

A. Interim analysis for the initial safety review

A) When the 10th subject is allocated to A+B arm and finishes his/her Week 4 visit, an evaluation will be performed on 10 subjects in A+B arm for incidence, types, and grades of surgical site infections, wound dehiscence, and other adverse events.

B) Evaluation results will be reported to IRB. If incidence, types, and grades of adverse events are judged to exceed the usual range, possible measures including trial discontinuation will be considered.

B. Interim analysis for wound dehiscence of subcutaneous drain

A) An evaluation will be performed when the 44th subject of A+C arm and B+D arm, respectively, completes his/her week 4 visit.

B) If wound dehiscence incidence of A+C arm is lower than B+D arm (one-sided p < 0.005), it will be decided that subcutaneous drain insertion reduces wound dehiscence and further randomization will be stopped. That is to say that subcutaneous drain will be inserted to all subject from then.

1. **Investigational Product Dosage, Application/Administration Methods, Combination Therapy, and Reasons for Comparator (as applicable)**

(1) SS-PDS arm (fascia closure using SS-PDS)

A. Instructions

A) STRATAFIX Symmetric PDS Plus, suture size: 1/0, suture length: 45cm, needle size: 40mm (CT needle) (Ethicon, Somerville, NJ, USA)

B) Running suture will be used as recommended by the manufacturer and stated in previous studies [PMID: 28603661] (<https://www.youtube.com/watch?v=PTYtYvSaGMg>, <https://youtu.be/TPyulS4fQgQ>)

C) Peritoneum closure should be performed. If peritoneum closure is impossible due to peritoneotomy, it may not be performed.

D) For fascia closure, stiches will be made 5-8 mm apart including 5-8 mm thick tissues on both sides of the incision surface.

E) It is allowed to make additional stiches for fascia closure with a few interrupted sutures using PDS or other sutures based on the investigator’s judgment.

F) Suture length is recommended to be 4 times longer than the skin incision. That is, if the skin incision is 20cm, it is recommended to use 80cm or longer suture for closure.

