Use of subcutaneous can be regarded as one of standard techniques. Therefore, it is judged that there will be no additional side effects/risks compared to standard treatments.

(2) Statement of rationale (or expected scientific/medical benefits) for continuing the trial despite predictable side effects/risks

It is judged that expected benefits from the trial (incisional hernia can be reduced by using SS-PDS for abdominal fascia closure) outweigh potential side effects/risks (increased incisional hernia, surgical site infections, wound dehiscence, and pains in SS-PDF arm) from the trial.

1. **Discontinuation Criteria and Dropouts from Study**

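### Drain harms other than infection and dehiscence have no valid planned comparison, and the drain interim can end drain randomisation on dehiscence alone

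*Protocol*

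**What the plan says.** **Allocation.** Under Control Group Setting and Randomization, SS-PDS against conventional suture and drain against no drain are each randomised 1:1. A+B is the SS-PDS group. The interim rule shows that A+C is the drain group.

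**Causality.** Under (1) Causality Evaluation, the only question asked is about the suture: "Investigators will determine that there is or there is no causal relationship with the SS-PDS use (including control group’s suture"). For doubtful events, "If it is difficult for the investigator to make a judgment, it will be judged to have a causal relationship". For the drain, "Causality will not be evaluated for the use of subcutaneous drain".

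**Comparisons.** Objective I compares adverse events other than hernia, pain, SSI and dehiscence between A+B and C+D. The Overview's safety assessment is also by suture. Objectives G and H compare SSI and dehiscence by drain. Under (2) Evaluation Methods in the safety section, all four items compare suture-related events between A+C and B+D.

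**Drain interim.** Under (8) Interim Analysis, part B: "An evaluation will be performed when the 44th subject of A+C arm and B+D arm, respectively, completes his/her week 4 visit". The rule reads "If wound dehiscence incidence of A+C arm is lower than B+D arm (one-sided p < 0.005), it will be decided that subcutaneous drain insertion reduces" that outcome. Drain randomisation then stops: "That is to say that subcutaneous drain will be inserted to all subject from then". No other outcome is mentioned.

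**Rationale.** The risk section treats the drain as a standard technique: "Therefore, it is judged that there will be no additional side effects/risks compared to standard treatments". The Background is less settled: "Opinions vary as to whether subcutaneous drain insertion at the time of abdominal closure reduces wound dehiscence".

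**The concern.** A drain can reduce dehiscence and still cause other problems. The protocol places it through its own skin perforation and allows it to remain beyond 14 days. For a harm that is neither SSI nor dehiscence, such as bleeding at the drain site, there are two possible records. If the investigator is unsure, it counts as suture-related. If the investigator correctly judges it unrelated to the suture, it falls outside every comparison listed under (2) Evaluation Methods. Neither record identifies a drain effect, and no comparison of all adverse events by drain is planned.

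The interim adds to this. Its rule commits the remaining subjects to a drain on one outcome, although the same Week 4 visit also supplies SSI and adverse events. At stake are what the trial can say about drain safety and whether an irreversible design change is made on part of the available evidence.

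**Working it through.** **1. Which comparison covers which drain harm**

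| Harm | Final comparison by drain | At the drain interim |
| --- | --- | --- |
| Dehiscence | Yes (objective H), no causality filter | Yes, benefit direction only |
| SSI | Yes (objective G), no causality filter | Not planned |
| Other events judged suture-related, including doubtful ones | A+C vs B+D, in conflict with objective I | Not planned |
| Other events judged not suture-related | None | Not planned |

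The adverse-event row of the efficacy table names no arms, so it does not fill the last row. The early safety review covers 10 A+B subjects and is not split by drain. The efficacy table also gives the SSI comparison by drain a Day 4 limit where objective G says Week 4; those two need reconciling.

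**2. The conflict over arm labels**

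Take assumed suture-related rates of 15% (SS-PDS) and 5% (control), and a drain-event rate of 10%, all booked to the suture.
- Drain group: the mean of 1 − 0.85 × 0.90 = 23.5% and 1 − 0.95 × 0.90 = 14.5%, which is 19%.
- No-drain group: the mean of 15% and 5%, which is 10%.
- With no drain events, the contrast is 10% against 10%.

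As written, the comparison cancels a 10-point suture effect and shows only drain effects. If it is relabelled A+B against C+D to match objective I, the only adverse-event contrast by drain disappears.

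**3. Subjects affected by a switch**

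The stated total reproduces. With the arcsine formula, h = 2·asin(√0.13) − 2·asin(√0.03) = 0.3896. At one-sided 0.05 and power 0.8, n = 2(1.645 + 0.842)²/h² = 81.5, and 81.5/0.94 = 86.7, so 87 per arm and 174 in all. The point here does not depend on it.

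Inputs: 88 subjects at the look, 9 enrolled per month, Week 4 window of 3 to 5 weeks, 4.345 weeks per month. Enrolled by then = 88 + 9 × weeks/4.345.
- 3 weeks: 94.2 enrolled, 79.8 left
- 4 weeks: 96.3 enrolled, 77.7 left
- 5 weeks: 98.4 enrolled, 75.6 left

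About 76 to 80 subjects would be enrolled without drain randomisation. The no-drain group would stay near 47 to 49 (half of 94 to 98), with no concurrent controls for later subjects.

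**4. When the rule fires**

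Exact binomial enumeration at 44 per arm, one-sided p < 0.005. The protocol gives no dehiscence rates, so these are assumptions.

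| No drain | Drain | Chi-square | Fisher |
| --- | --- | --- | --- |
| 10% | 10% | 0.3% | 0.1% |
| 20% | 20% | 0.4% | 0.2% |
| 20% | 10% | 8.8% | 5.5% |
| 30% | 10% | 40% | 32% |
| 10% | 20% | 0.004% | 0.001% |
| 20% | 30% | 0.012% | 0.005% |

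A drain that worsens dehiscence is effectively protected against. A drain that lowers dehiscence and raises something else is not.

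**5. What an SSI look could show**

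At 44 per arm, one-sided 0.05, assumed rates: power is 24% for 5% vs 10%, 38% for 10% vs 20%, and 72% for 5% vs 20%. A formal SSI test would often miss real harm, so a reviewed table suits the purpose better than a significance gate.

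**The case against.** The case against is substantial, and most of it limits how far the point goes.

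- A reader might infer that drain harm cannot be seen. That is not supported. Dehiscence by drain is what the interim examines, drain allocation is open, eCRF data are reviewed monthly, and all adverse events go to the IRBs yearly. What is missing is a planned review by drain.
- A reader might infer that no objective asks about drain harm. Objectives G and H do, without any attribution step. The gap concerns other adverse events.
- A reader might infer that all drain harm is booked to the suture. Investigators may record no relationship; the default applies only where judgement is difficult. SSI and dehiscence are outside objective I altogether.
- A reader might argue that a true SS-PDS difference is badly diluted. If suture-related rates were 20% and 10%, adding 5 points to each arm gives 25% and 15%, so the ratio falls from 2.0 to 1.67; adding 10 points gives 30% and 20%, ratio 1.5. These rates are assumed, every drain event is taken as booked to the suture, and the absolute difference stays at 10 points. Some power could be lost, but the drain is balanced across sutures, so there is no bias against either. As written, the suture-related comparison is not by suture at all.

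Two further arguments carry less weight. Interim safety tables are often left to the analysis plan, but here the protocol itself fixes a decision on one outcome. The drain may be a standard technique, but the protocol randomises it because its value is disputed, so an assumption of no added risk is a weak reason not to compare.

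**Conclusion.** The point holds in a limited form. Drain harms other than SSI and dehiscence have no valid planned comparison, and the one adverse-event contrast that uses the drain grouping is restricted to suture-related events and contradicts objective I. The interim can end drain randomisation on lower dehiscence alone.

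The consequence is conditional. It needs the rule to fire, which ranges from under 1% with equal dehiscence rates to roughly 30 to 40% with an assumed fall from 30% to 10%, and it needs a simultaneous excess of SSI or other events. If both occur, about 76 to 80 later subjects are affected, assuming the stated enrolment rate, even filling of the drain arms and no delay between the look and the decision. The primary hernia comparison is not called into question. This is an inexpensive improvement worth making.

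**What to change.** 1. At the 44 + 44 interim, tabulate Week 4 SSI and all-cause adverse events for A+C against B+D alongside dehiscence. State who reviews the table, and that the review precedes any decision to end drain randomisation.
2. Add an all-cause A+C versus B+D adverse-event summary to the final analysis. If the rule has fired, show separately the subjects enrolled while the drain was still randomised.
3. Reconcile the arm labels under (2) Evaluation Methods with objective I (A+B versus C+D). Do this together with item 2, since relabelling alone would remove the only adverse-event contrast by drain.
4. Optionally, record drain-relatedness as a separate item for subjects who received a drain, so that a doubtful drain event is not recorded only as suture-related.

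The first three items use data already collected and cost one interim table, one final table and a text correction. The fourth costs one eCRF field. Its weakness is that attribution for an open-label drain is subjective, so the all-cause tables should carry the main weight.
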